### Data collection

At baseline, general characteristics of patients including age, gender, medications used, and underlying chronic diseases are collected by investigators using a paper-based record system. All outcomes of interest (clinical symptoms and laboratory markers) are assessed at baseline and at the end of the intervention period (3 weeks later).

Data entry will be done by one of the blind research team members and a double check is performed by another blinded team member. Written informed consent is collected for each patient at the beginning of the study by investigators. Dietary supplements and biochemical tests are provided free of charge for participants to increase their willingness to participate in the study. Data protection was done by keeping the identity of the patients anonymous by excluding their names throughout the study.

After an overnight fast (10–12 h), 10 ml venous blood samples are taken from patients in the morning. First, 4 ml blood is collected in ETDA tube (1 mg/ml) and used for complete blood cell (CBC) count. The remaining 6 ml blood is allowed to clot for 45 min at room temperature; serum is then isolated by centrifugation at 3000 rpm for 10 min and stored at – 70 °C until analysis. Blood samples are collected and assayed by lab investigators that are blinded to the patient assignments.

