**Participants:**

This study is conducted on COVID-19 patients admitted to the Shahid Mohammadi hospital in Bandar Abbas, Iran, who are eligible for inclusion in the study. Patients are included only if they meet all of the following criteria: (1) aged from 18 to 65 years old; (2) confirmation of COVID-19 by RT-PCR test; (3) completing informed consent; (4) passing less than 48 h since the patient's hospitalization; (5) no skin or gastrointestinal allergies due to taking multivitamin supplements, vitamin D, and magnesium; and (6) having more than 30 breaths per minute and less than 93% oxygen saturation in room air and sea level. Patients are excluded if they have any of the following conditions: (1) pregnancy or lactation; (2) taking a daily multivitamin or take a vitamin D or magnesium supplement in the last month; (3) participating in other clinical trials; (4) renal failure or dialysis, severe liver disease or cirrhosis; (5) known diagnosis of hypercalcemia; (6) discharging from the hospital less than 24 h after the start of the intervention; (7) history of kidney stones in the last year; (8) transfer the patient to the ICU; (9) baseline vitamin D levels above 80 ng/ml; (10) baseline magnesium levels above 2.6 mg/dl; and (11) unwillingness of the patient to continue the study.

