**Main outcomes:**

The resolution of clinical symptoms (fever, dry cough, shortness of breath, headache, myalgia, oxygen saturation, and mortality rate) and interpretation of laboratory assays (CRP, MDA, TAC, WBC, neutrophils count, lymphocytes count, ratio of neutrophils to lymphocytes, levels of 25 hydroxyvitamin D and magnesium) will be assessed in the study groups.

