### Intervention and comparator

Participants will be randomly allocated to one of the four following groups: (A) vitamin D (two 50,000 IU capsules at the beginning of the study, two 50,000 IU capsules on the 4th day, one 50,000 IU capsule on the 11th day, and one 50,000 IU capsule on the 17th day) and magnesium supplement (300 mg/day); (B) vitamin D capsule and magnesium placebo; (C) magnesium supplement and vitamin D placebo; and (D) vitamin D placebo and magnesium placebo.

To ensure patient compliance with the assigned treatment, the subjects are monitored weekly by telephone and, if necessary, in-person visits. The compliance rate will be calculated according to the number of delivered and returned capsules by the following formula: number of capsules delivered − number of capsules returned/number of capsules delivered.

The criteria for discontinuation are any medical complications during supplementation or at the request of the patient. However, there is no possibility of harm to participants due to the type of dietary intervention. If the assigned intervention is discontinued for any reason, the patient has to be excluded from the study.

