### Main outcomes

The resolution of clinical symptoms and interpretation of laboratory assays will be assessed in the study groups.

Clinical symptoms:FeverDry coughShortness of breathHeadacheMyalgiaOxygen saturationMortality rate

Laboratory markers:C-reactive protein (CRP)Malondialdehyde (MDA)Total antioxidant capacity (TAC)White blood cell (WBC)Neutrophils countLymphocytes countThe ratio of neutrophils to lymphocytesLevels of 25 hydroxyvitamin D and magnesium

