### Statistical analysis

The Kolmogorov–Simonov test will be used to check the normality of variable distribution. One-way ANOVA and Bonferroni post hoc tests will be used to analyze the differences between groups.

The mixed linear model will be used to estimate the treatment effect and the possible confounding variables will be adjusted in the model. IBM SPSS version 22 will be used for statistical analysis. *P*-value ≤ 0.05 will be considered a significant level in all statistical tests. To handle protocol non-adherence, the intention-to-treat (ITT) principle will be used to analyze data based on the original treatment assignment of the patients. Variables will be expressed as mean ± standard error or 95% confidence interval. The research team will not conduct interim analyses to stop or extend the trial because of the low-risk nature of the nutritional intervention in the present study. Indeed, early detection of the study hypotheses is unlikely and early termination of the intervention is not supposed to have any additional protection for patients.

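### Symptoms and SpO2 have one follow-up reading, at week 3, and no rule for deaths, so the comparison defaults to survivors and completers and can be biased if treatment affects survival

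*Protocol article*

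**What the plan says.** All places are in the protocol article.

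- **Timing (Data collection):** "All outcomes of interest (clinical symptoms and laboratory markers) are assessed at baseline and at the end of the intervention period (3 weeks later". No assessment between these two is described.
- **Outcomes (Main outcomes):** "The resolution of clinical symptoms and interpretation of laboratory assays will be assessed in the study groups". The clinical list in the Abstract reads "fever, dry cough, shortness of breath, headache, myalgia, oxygen saturation, and mortality rate". Death is thus one item beside five symptoms and SpO2. The article does not say how a death counts towards the other items.
- **Entry severity (Participants):** "more than 30 breaths per minute and less than 93% oxygen saturation in room air and sea level".
- **Exclusions:** the list in Participants includes "8) transfer the patient to the ICU". Intervention and comparator adds: "If the assigned intervention is discontinued for any reason, the patient has to be excluded from the study".
- **Analysis (Statistical analysis):** one-way ANOVA with Bonferroni comparisons, and a mixed linear model with covariate adjustment. As the answer to non-adherence, "the intention-to-treat (ITT) principle will be used to analyze data based on the original treatment assignment of the patients".

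**The concern.** A patient who dies in the first three weeks has no fever, cough, dyspnoea, headache, myalgia or SpO2 reading at week 3. ITT keeps that patient in the assigned group but cannot supply the reading. ITT is also invoked here for non-adherence, and death is not non-adherence.

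Survival is itself an outcome of treatment. If one arm has fewer deaths, its week-3 group contains patients who would have died on the other arm, and these may be among the sickest. A comparison among those still alive then sets different kinds of patients against each other and loses the protection of randomisation. An effect on survival could make symptom resolution look worse than it is, or hide a benefit.

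The exclusion of patients whose intervention stops works in the same direction. It turns the survivors into survivors who also completed treatment, and it may remove patients before their death is counted under mortality.

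**Working it through.** **Step 1. What each stated method does with a death before week 3.**

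- ANOVA on week-3 values, or on change from baseline: there is no value, so the patient drops out.
- Mixed linear model with two occasions: the patient contributes the baseline reading at most. There is no earlier follow-up reading to carry information. The week-3 value is treated as existing but unobserved, and it is inferred from survivors with a similar baseline.
- Exclusion on discontinuation, if applied: the patient is out of both.

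So the week-3 contrast rests on survivors' values under either method.

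**Step 2. Inputs for the size.**

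- From the article: 104 patients, 26 per group, factorial design. Each factor therefore compares 2 × 26 = 52 with 52.
- Not in the article: death rates and resolution rates. There is no stated figure to reproduce. The 10% dropout allowance in Sample size does not say whether deaths are included. Everything below is an assumed range.

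Let pc and pt be the death rates in the control and treated arms, r0 the resolution rate in patients who survive on either arm, and q the resolution rate in patients saved by treatment. Treatment is taken to have no effect on symptoms otherwise.

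- Survivors only: difference = (pc − pt)(q − r0) / (1 − pt)
- All randomised, death counted as not resolved: difference = (pc − pt) × q

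**Step 3. Worked counts, 52 vs 52.**

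*Deaths 10 vs 5; 32 control survivors resolve; 1 of the 5 extra survivors resolves.*

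- Survivors: 32/42 = 76.2% vs 33/47 = 70.2%, difference −6.0 points.
- All randomised: 32/52 = 61.5% vs 33/52 = 63.5%, difference +1.9 points.

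*Deaths 5 vs 3; 36 control survivors resolve; 20% or 50% of the 2 extra survivors resolve (expected counts).*

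- Survivors: 36/47 = 76.6% vs 36.4/49 = 74.3% or 37/49 = 75.5%, difference −2.3 or −1.1 points.
- All randomised: 36/52 = 69.2% vs 36.4/52 = 70.0% or 37/52 = 71.2%, difference +0.8 or +1.9 points.

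These counts treat all 52 patients per level as having the symptom at baseline. For a symptom that only some had, the counts shrink. The percentages stay the same only if deaths and resolution are spread alike.

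**Step 4. Range, with r0 = 80%.**

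| Deaths, control vs treated | q | Survivors only (points) | Death as not resolved (points) |
|---|---|---|---|
| 5% vs 2% | 0 | −2.4 | 0 |
| 5% vs 2% | 40% | −1.2 | +1.2 |
| 10% vs 5% | 0 | −4.2 | 0 |
| 10% vs 5% | 40% | −2.1 | +2.0 |
| 20% vs 10% | 0 | −8.9 | 0 |
| 20% vs 10% | 40% | −4.4 | +4.0 |
| any row above | 80% | 0 | +2.4, +4.0, +8.0 |

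The rows with q = 0 are the extreme in which no saved patient resolves. The bias is nil when q = r0 or pc = pt.

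**Step 5. With a true 5-point symptom benefit in patients who survive on either arm (85% vs 80%), q = 0.**

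- 10% vs 5% deaths: (0.90 × 0.85)/0.95 = 80.5%, difference +0.5 points. Most of the benefit is hidden, but the sign holds.
- 20% vs 10% deaths: (0.80 × 0.85)/0.90 = 75.6%, difference −4.4 points. The sign reverses.

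No figure is given for SpO2, because the article states no mean or spread for it.

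**The case against.** The strongest reply is that nothing in the article prescribes a survivors-only analysis. It states ITT and a mixed model, it describes itself as a summary of a fuller protocol that is not at hand, and a rule for deaths may stand there or in an analysis plan. That is fair, and a reader who infers a written survivors-only rule goes beyond the text. What stands is narrower. The article does fix the outcomes, the single follow-up time, the models and an exclusion on discontinuation, and a patient who dies has no value under that combination. What counts as resolution is part of the outcome definition.

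A second reply is that in-study deaths may be few. Age is capped at 65, renal failure and severe liver disease are excluded, and ICU transfer may remove many patients before they die. This also stands, and it limits the expected size. But if the ICU and discontinuation exclusions are what keeps deaths out, they do so by selecting after randomisation, against the ITT statement and at the expense of the mortality item.

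A third reply is that mortality is reported anyway, so a reader could see an imbalance. That protection is weak. With 52 vs 52, power to detect 20% vs 10% deaths is about 30%, and for 10% vs 5% about 16% (two-sided 5%, rates assumed).

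A fourth reply is that a composite lets a mortality difference appear as an effect on headache or myalgia. That is a real cost, and it is why the components should be shown. The laboratory markers have the same gap after death. The point is confined to symptoms and SpO2, where placing death as the worst result has a plain meaning.

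**Conclusion.** The point holds in a conditional form. The schedule, outcome list, models and exclusion rule together default to a comparison among survivors and completers, and that comparison can be biased if treatment affects survival. In the worked counts the survivor comparison is about 1 to 6 points against the arm with fewer deaths, with deaths of 5 vs 3 up to 10 vs 5 of 52. The wider range reaches about 9 points only at 20% vs 10% deaths with no saved patient resolving.

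All of this rests on assumed death and resolution rates, on a treatment effect on mortality, and on saved patients resolving less often than other survivors. Under this model there is no bias if deaths are equal or saved patients resolve as often as the rest.

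A reader might infer that a life-saving effect will show up as worse symptom resolution. The documents do not support that. They give no death rate, and a true symptom benefit can outweigh the bias at low mortality.

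**What to change.** 1. In Main outcomes, define each symptom outcome as alive and free of that symptom at day 21. The denominator is all randomised patients who had the symptom at baseline, and death before day 21 counts as not resolved.
2. Compare SpO2 at day 21 by ranks, with patients who died placed below the lowest observed value.
3. Keep mortality as a separate item in all randomised patients, and show survivor-only symptom and SpO2 figures descriptively.
4. Reconcile the ICU-transfer criterion in Participants and the exclusion on discontinuation in Intervention and comparator with the ITT statement in Statistical analysis, so that deaths after these events are counted.

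**Cost:** wording in the outcome and analysis sections, plus an amendment and registry update, made before the group codes are released. No new measurement is needed, since mortality is already an outcome; vital status at day 21 would have to be obtained for any patient already removed under the exclusion rules. Each symptom outcome becomes a death-or-symptom composite, and its denominator is smaller for symptoms that only some patients had at entry.

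### Mortality, and symptom resolution as worded, are yes/no outcomes, but the article names only continuous-outcome methods and summaries, which give the wrong denominator, no usable model for death and zero-width uncertainty in arms without events

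*Protocol article*

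**What the plan says.** Under Main outcomes the article states that "The resolution of clinical symptoms and interpretation of laboratory assays will be assessed in the study groups". The abstract lists the clinical outcomes as "fever, dry cough, shortness of breath, headache, myalgia, oxygen saturation, and mortality rate". No measurement scale is given for the five symptoms, and resolution is not defined further.

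Under Data collection the timing is fixed for every outcome, symptoms and laboratory values alike: they "are assessed at baseline and at the end of the intervention period (3 weeks later").

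Under Statistical analysis, after a normality check, two analyses are named. The first is the comparison of the arms: "One-way ANOVA and Bonferroni post hoc tests will be used to analyze the differences between groups". The second is a regression model, introduced directly afterwards: "The mixed linear model will be used to estimate the treatment effect and the possible confounding variables will be adjusted in the model".

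For presentation, "Variables will be expressed as mean" with a standard error or a 95% confidence interval. No outcome is exempted. No categorical, logistic or time-to-event method is named, and no counts or proportions are mentioned.

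Under Intervention and comparator, "the subjects are monitored weekly by telephone". The stated purpose is compliance.

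**The concern.** Clinical symptoms come first in the title and the aim, yet every method named is for a continuous outcome. Followed as written, the plan has three consequences for the binary outcomes.

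- **Denominator.** A symptom can resolve only in a patient who had it. The entry criteria require rapid breathing and low saturation, but not fever, cough, headache or myalgia. A mean over a whole arm therefore mixes patients who recovered from a symptom with patients who never had it.
- **Model.** Every patient is alive at baseline. A repeated-measures linear model over baseline and week 3 has no baseline variation to use for death.
- **Uncertainty.** In an arm with no deaths, or with every symptom resolved, the sample standard deviation is zero. The reported standard error and confidence interval then have zero width, although such an arm still carries real uncertainty.

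Timing is a related but separate matter. A single week-3 reading shows whether recovery has occurred, not how fast. The patients are already telephoned every week.

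**Working it through.** The article gives no figure for any binary outcome to reproduce, because its sample size rests on malondialdehyde alone. It also gives no expected resolution or death rate, so every rate below is an assumption, shown as a range.

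**Inputs from the article:** four arms of 26, with dropout 0.1, so about 26 × 0.9 = 23.4, taken as 23 per arm.

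**1. Chance that at least one arm has no deaths.** With a common death probability p and n patients per arm, one arm is empty with probability (1 − p)^n, and at least one of four with probability 1 − [1 − (1 − p)^n]^4.

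| p | n = 23: one given arm | n = 23: at least one of four | n = 26: at least one of four |
|---|---|---|---|
| 2% | 0.98^23 = 0.628 | 1 − 0.372^4 = 98% | 97% |
| 5% | 0.95^23 = 0.307 | 1 − 0.693^4 = 77% | 71% |
| 10% | 0.90^23 = 0.089 | 1 − 0.911^4 = 31% | 23% |

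The same figures apply to an arm with complete resolution when the resolution rate is 98%, 95% or 90% and all n patients had the symptom. With fewer symptomatic patients the chance is higher.

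**2. What such an arm would show.** With 0 events in 23, the mean is 0 and the standard error is √(0 × 1/23) = 0, so the report is 0 ± 0 with an interval from 0 to 0. The score (Wilson) upper limit is z²/(n + z²) = 3.84/(23 + 3.84) = 14.3%. The same data are therefore compatible with a death risk of up to about 14%.

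**3. Effect of the denominator.** Let a share q of each arm have the symptom at baseline, with resolution r1 and r2 among them, and ignore new symptoms. Over the whole arm the difference in week-3 symptom prevalence is q(r2 − r1). For illustration, with q = 0.5 and resolution of 50% against 80%, it is 0.5 × 0.30 = 15 points, not the 30 points among patients who could resolve.

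**4. Does ANOVA on 0/1 data raise the false-positive rate?** These are simulated rejection rates with four arms of 26 and equal true rates (200,000 runs).

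| Common rate | ANOVA | Chi-square |
|---|---|---|
| 50% | 5.2% | 5.1% |
| 80% | 4.8% | 4.6% |
| 90% | 4.1% | 3.7% |
| 95% | 3.9% | 3.1% |
| 98% | 1.5% | 1.5% |

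It does not. With 23 per arm, the chance that any Bonferroni pair is significant is about 0.1% at a 2% event rate and about 1% at 5%. The procedure is conservative for rare events.

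**The case against.** **The article is a summary.** It says that a fuller protocol is attached, and the section opens with a normality check, so it can be read as describing continuous variables only. A categorical test may be named elsewhere. This has some force. But the text does more than stay silent: it names the methods and the summary format without exempting any outcome, and two of the listed main outcomes do not fit them.

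**The yes/no scale is inferred.** This stands for the symptoms. It comes from the word resolution, and a severity score would change the method needed. It does not touch mortality, which is binary on any reading. Oxygen saturation, in the same list, is continuous and properly handled by a linear model.

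**A reader might infer that the planned tests are invalid.** The simulation does not support this. ANOVA on 0/1 data behaves much like chi-square, and a linear model on 0/1 data estimates a risk difference. Nor is the low Bonferroni rate for rare events an argument for Fisher tests: Bonferroni-corrected Fisher tests on the same layout reject even less often (about 0% at 2% events, 0.004% at 5%).

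**A reader might infer a proven ceiling at week 3 that leaves almost no power.** The documents give no resolution rate, and entry requires fairly severe illness, so 90% or more resolved is an assumption. For 90% against 97%, Fisher power is 4% (23 per group) and 12% (46 per group), but a t-test on the same data gives 10% and 30%, so part of the shortfall belongs to Fisher's test. Setting that 7-point gap beside an early gap of 50% against 80% (Fisher power 46% and 82%) is not like for like. With 7 points early (50% against 57%), Fisher power is 4% and 7%, no better than at the ceiling.

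**Weekly symptom readings are a design addition.** This also stands. Week-3 status is a legitimate endpoint, and recruitment was expected to finish by the end of August 2022, before the article appeared in February 2023. Few or no patients may remain to benefit.

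**Conclusion.** The point holds in limited form. As written, the analysis section gives mortality, and symptom resolution if recorded as yes/no, unsuitable summaries, denominators and models. The firmest part is mortality: no baseline value, and a 77% to 98% chance of at least one 0 ± 0 arm of 23 if true mortality is 5% to 2%, falling to 31% at 10%. The symptom part rests on the yes/no reading. The documents do not support a claim of excess false positives, and the size of any ceiling at week 3 is unknown.

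The single late reading is a separate limitation: it cannot show faster recovery, and changing the test does not cure that. The malondialdehyde comparison is unaffected. The matter should be corrected, but it does not undermine the trial as a whole.

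**What to change.** In the analysis section, before the treatment codes are released:

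1. State how each symptom is recorded and what counts as resolved, including how a patient who dies before week 3 is counted.
2. Report binary outcomes as counts and proportions per arm, not as mean and standard error.
3. Analyse each binary symptom among patients who had it at baseline, by logistic regression with vitamin D and magnesium terms. Use a Firth-type penalty where an arm has no events or all events. Give risk differences with score-type 95% confidence intervals.
4. Analyse week-3 mortality in all randomised patients by the same penalised or an exact approach, in line with the article's own intention-to-treat statement.
5. Keep the linear models for oxygen saturation and laboratory values.

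This costs analysis wording only and needs no new data, provided that baseline symptom status and week-3 vital status are recorded as planned. Subsets symptomatic at baseline will be smaller than the full arms, so intervals will be wide, and exact methods are conservative.

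As an optional improvement for patients still to be enrolled, record the five symptoms at the existing weekly calls and compare resolution over weeks 1 to 3, for example with a discrete-time survival model. This costs about a minute per call. If recruitment has closed, report the single week-3 reading as a limitation.
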